#### Selection of local organizations and allocation of workshops

First, we looked for local organizations who would volunteer to host the workshops as part of the ALAPAGE study. The research team, with support from its operational partners (e.g., the regional retirement fund) launched the call for applications to invite local organizations to participate in the study. Local organizations who were interested in the study filled out an information sheet (requesting information such as location, number of older people in their active file, experience in organizing prevention workshops, period of availability to organize one or more workshops, availability of a “point-of-contact” person to manage the logistical aspects of the workshops, the provision and storage of materials, etc.) and returned it to the research team. A total of 45 local organizations submitted proposals between June 1, 2021 and July 16, 2021. The research team and its operational partners then selected 25 out of the 45 organizations to host a total of 45 workshops. The selections were based on a reasoned choice and operational criteria (e.g., availability, materials, and staff resources).

We performed a block randomization with the use of computer-generated randomization lists. We created four time-based blocks (start date of the workshop); each observed a 2:1 allocation ratio. We did this to take into account the seasonality of both diet and physical activity behaviors in addition to any potential disruptions due to the COVID-19 pandemic (block 1: 12 workshops between January 2022–April 2022; block 2: 12 workshops between May 2022–October 2022; block 3: 15 workshops between November 2022–April 2023; block 4: 6 workshops between May 2023–June 2023).

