### Data analysis

All statistical analyses will be performed using SAS 9.4 (SAS Institute Inc., Cary, NC, USA). A α of 0.05 will be used to determine statistical significance.

First, descriptive statistics (mean ± standard deviation, median, and frequency distribution) will be carried out to describe baseline characteristics (sociodemographic, life conditions, primary and secondary outcomes) of participants in both groups. To compare the baseline characteristics (age, gender, life conditions) between the two groups, a one-way ANOVA or a Kruskal-Wallis test will be used for continuous variables and a Chi-square or a Fisher’s exact test will be used for categorical variables.

As part of the effectiveness evaluation, linear or logistic (depending on the nature of the dependent variable) mixed models will be carried out to study the impact of the intervention on primary and secondary outcomes, while taking into account the repeated nature of the data and the intra-cluster correlation. Time, group and their interaction will be defined as fixed factors (see Additional file 7 for more details). If imbalances occur between the groups, the baseline values will be added as covariates in the models. Missing data will be inspected, and, if appropriate, will be handled using multiple imputation.

As part of the process evaluation, we plan to perform mediation analyses to verify whether beliefs, attitudes, and intention are pathways by which the intervention impacts physical activity. Furthermore, we plan to perform moderating analyses to test whether the effect of the intervention varies according to some characteristics (in particular, type of recruitment, antecedents of physical activity or history of falls, and baseline dietary diversity).

As part of the process evaluation, qualitative data from participant interviews of the intervention group will be transcribed and analyzed using a data-driven inductive approach to explore how the intervention may have resulted in behavioral changes.

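### Workshops are randomised within four start-date blocks because of seasonality, but the stated fixed factors include no block term, so precision may be lost where the T0–T2 change varies by season

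*Protocol article*

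**What the plan says.** Under *Selection of local organizations and allocation of workshops*, the protocol article describes the randomisation: "We created four time-based blocks (start date of the workshop); each observed a 2:1 allocation ratio". The reason given is "to take into account the seasonality of both diet and physical activity behaviors", together with possible disruption from COVID-19. The blocks hold 12, 12, 15 and 6 workshops, the last being "block 4: 6 workshops between May 2023–June 2023".

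Under *Data analysis*, the effectiveness outcomes are to be analysed with linear or logistic mixed models that allow for repeated measurement and for correlation within workshops. On the fixed part the article says: "Time, group and their interaction will be defined as fixed factors", and refers to Additional file 7 for more detail. Baseline values join as covariates only if the groups turn out to be imbalanced. The article nowhere names block, start date or season as a term in the analysis.

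**The concern.** The design treats start date as prognostic, and the listed model then leaves it out. Stratifying removes block variation from the true sampling error of the group comparison. If the model is not told about the blocks, that variation can remain in the estimated error, so the stratification is paid for but not used. Reported intervals could then be wider, and power lower, than the design allows.

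The effect of interest is a difference in change over time. What counts is therefore whether the change differs between blocks, not whether the level does.

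**Working it through.** **Inputs from the article.** There are 30 intervention and 15 control workshops of 10 people, with 30% dropout (7 completers per workshop), an ICC of 0.03, α = 0.05 and 95% power for both primary outcomes. The assumed dietary diversity effect is +1 SD (*Sample size calculation*). The chair-stand effect size is not given as a number.

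**Assumptions, because the article gives no figure.** Tests are two-sided; within-person correlation is 0.5, so the variance of change is 2 × (1 − 0.5) = 1 in SD² units; the ICC of 0.03 applies to change; and the between-block SD of mean change, τ, is 0.1, 0.2 or 0.3.

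**1. Balance.** A 2:1 split gives 8:4, 8:4, 10:5 and 4:2, which totals 30:15. Each block has the same weight in both arms (8/30 = 4/15, 10/30 = 5/15, 4/30 = 2/15). A block effect on the change therefore cancels from the estimated group difference, so there is no bias by design and the true SE does not depend on τ.

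**2. The stated 95% power.** The variance of a workshop's mean change is 0.03 + 0.97/7 = 0.1686. The true SE is √[0.1686 × (1/30 + 1/15)] = 0.130. Power of 95% needs an effect of (1.960 + 1.645) × 0.130 = 3.605 × 0.130 ≈ 0.47 SD. At +1 SD, the effect divided by its SE is 1/0.130 = 7.7 and power exceeds 99.9%. The stated 95% therefore does not come from dietary diversity on these inputs. It may come from chair stand, but that cannot be checked.

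**3. Random workshop-by-time effect in the model, block-by-time omitted.** The model then sees a workshop variance of 0.1686 + τ². The SE ratio is R = √[(0.1686 + τ²)/0.1686]. Because the true SE is unchanged, power is Φ(3.605 − 1.96R) and actual type I error is 2 × [1 − Φ(1.96R)].

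| τ | Reported SE | R | Power from a 95% start | Actual type I error |
|---|---|---|---|---|
| 0 | 0.130 | 1.00 | 95% | 5.0% |
| 0.1 | 0.134 | 1.03 | 94% | 4.4% |
| 0.2 | 0.144 | 1.11 | 92% | 2.9% |
| 0.3 | 0.161 | 1.24 | 88% | 1.5% |

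With a within-person correlation of 0.7, the inflation is about 5%, 18% and 38%. For dietary diversity at +1 SD, even R = 1.24 leaves Φ(7.7 − 1.96 × 1.24) = Φ(5.3), still above 99.9%.

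**4. Random intercepts only, block-by-time omitted.** The reported SE is about √[(1 + τ²)/7 × 0.1], that is 0.120, 0.122 and 0.125 for τ = 0.1, 0.2 and 0.3. If change has no workshop correlation, the true SE is √(0.1/7) = 0.1195 and the inflation is only 0.5%, 2.0% and 4.4%. If change has an ICC of 0.03, the true SE is 0.130 and the reported SE is too small by 7.5%, 6.1% and 3.9%.

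**5. Simulation check** (intercepts only, no workshop variance in change, 122 to 132 runs per scenario; only the mean SEs are used). With a seasonal level shift of ±0.3 SD and no difference in change, a block main effect leaves the mean SE at 0.1150. When the change also shifts by ±0.2 SD, adding block and block-by-time moves it from 0.1175 to 0.1152 (about 2%). At ±0.4 SD it moves from 0.1226 to 0.1142 (about 7%).

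**The case against.** The strongest reply is that the article refers to Additional file 7 for the model, and block may be specified there. That lowers confidence but does not remove the point: the article does list its fixed factors, and if the file adds block, the list should be aligned with it.

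It is also fair that the list is not the whole model, since clustering, repeated measures and conditional baseline adjustment are provided for. None of these carries block.

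The seasonal variance is assumed, and it may be zero. Block is a coarse proxy for season: blocks 1 and 3 both run to April, and blocks 2 and 4 both start in May. The stated seasonal rationale concerns diet and activity behaviours, not muscle strength, so nothing in the article shows that the chair-stand change is seasonal. All of this stands, and it is why the size is given as a range starting at zero.

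A reader might infer that all seasonal variance stays in the error and that the intervals are necessarily too wide. The documents do not support that. Seasonal levels cancel from the contrast, and the random structure is not stated; with intercepts only, the SE may even be too small.

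A reader might also infer that unequal workshop sizes or dropout let season leak into the group comparison. That is conceivable, but the article gives nothing from which to quantify it, and by design the blocks are balanced.

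**Conclusion.** The point holds as an unused design feature, with moderate confidence while Additional file 7 is unseen. The article stratifies on start date and lists fixed factors that omit it. The possible cost is precision; no bias by design is shown.

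The SE inflation is zero if change does not vary by season. It is about 3%, 11% and 24% for τ of 0.1, 0.2 and 0.3, given a random workshop-by-time effect and a within-person correlation of 0.5. From a 95% start, that means power of about 94%, 92% and 88%. With random intercepts only, the effect is smaller and the net SE error may go either way.

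It would be wrong to conclude that the trial is underpowered for dietary diversity, because at +1 SD its power stays above 99.9% throughout. Any loss concerns chair stand, whose effect size is not given, and the secondary outcomes.

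**What to change.** Before outcome data are seen, add randomisation block (four levels) and block-by-time as fixed effects in the linear mixed models. In a baseline-adjusted model of T2 alone, block is enough. In the logistic models, add the terms where the data support them. A block main effect by itself in the repeated-measures model would not help. If Additional file 7 already has these terms, align the article's list with it; if they are left out on purpose, give the reason.

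The cost is up to 3 degrees of freedom per time point and no new data, since the start block is known for every workshop. The weak spot is block 4, with two control workshops and about 14 control completers (2 × 7), where cells may be sparse for binary outcomes.

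The random part should be stated at the same time. With intercepts only and an ICC of change of 0.03, block-by-time would lower the reported SE to 0.1195 against a true 0.130, so the block terms do not cure that separate problem.

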### Outcomes

#### Effectiveness evaluation

Primary and secondary outcomes, with few exceptions, are assessed before the intervention (“T0”), at 6 weeks (“T1” corresponding to the end of ALAPAGE program’s session period) and then 3 months later (“T2”) (see Table 2 for an overview of outcomes and data time points).

**Table 2 Tab2:** Overview of outcomes and time point of data collection

TIME POINT		Week 1	Week 2	Week 3	Week 4	Week 5	Week 6	Week 7	Week 8	Week 18	Week 19
	I	S0	S1	S2	S3	S4	S5	S6	Home	Home	V3
		T0					T1			T2	
	C	V0	V1				Home	V2		Home	V3
		T0					T1			T2	

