***Cost-effectiveness evaluation***											
Costs	I	X	X	X	X	X	X	X	X		
	C	X	X	X	X	X	X	X	X		

*APA* adapted physical activity, *C* control group, *FFQ* Food Frequency Questionnaire, *I* intervention group, *S0-S6* diet and physical activity sessions of the ALAPAGE program, *T0-T2* evaluation time points, *V0-V3* measurement visits

^a^Lower limb muscle strength and other physical functions measured using the Senior Fitness Test battery are assessed at T0 and T2 but not at T1 because the interval time between T0 and T1 is too short to expect a significant impact of the intervention on these outcomes at T1

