We must also acknowledge some limitations. First, the recruitment of participants will take place after the randomization of workshops. This may lead to recruitment bias and a discrepancy in the characteristics of the participants in both the intervention and the control groups [68]. As part of this pragmatic cRCT, our operational partners did not find it feasible to recruit participants before the cluster randomization or by means of a blinded and independent person. To limit recruitment bias (e.g., participants in the intervention group are more interested in diet and physical activity issues and are thus more likely to change their behaviors than those in the control group), we will use a waiting-list control group design. Consequently, all participants are interested in participating in workshops on diet and physical activity. Second, due to feasibility constraints, the times points differ slightly between the intervention and control groups for some of the outcomes. However, we have done our best to limit these differences and to reconcile methodology requirements and practical feasibility. We hypothesize that this will have a limited impact on our results. Lastly, we cannot exclude differing attrition rates between the intervention and control groups that may lead to biased estimates of the intervention’s effects. In this instance, we plan to use appropriate econometric techniques (e.g., a Heckman sample selection correction model [69]) to correct for attrition bias [70].

The results of this study should help to implement public health interventions that are effective at improving dietary diversity, physical activity and fitness, and social outcomes among older people who live at home. They will contribute to the improvement of healthy aging while limiting social inequalities. The ALAPAGE program has been developed and will be evaluated in close relationship with major operational partners of healthy aging in France, thus providing a unique opportunity to expand its reach.

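### Adding baseline values only when the arms look unbalanced does not correct the group-by-time effect for chance imbalance, and in some models it understates the standard error

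*Protocol article*

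**What the plan says.** Under Data analysis, the effectiveness evaluation uses linear or logistic mixed models, "while taking into account the repeated nature of the data and the intra-cluster correlation". On the fixed part: "Time, group and their interaction will be defined as fixed factors", with Additional file 7 cited for detail. The next sentence is the rule at issue: "If imbalances occur between the groups, the baseline values will be added as covariates in the models". It does not say how large an imbalance must be, or which baseline values are meant.

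The same section plans between-group tests of baseline characteristics: "a one-way ANOVA or a Kruskal-Wallis test will be used for continuous variables", and chi-square or Fisher's exact tests for categorical ones. None of these allows for workshops.

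On timing, the Effectiveness evaluation section says: "Primary and secondary outcomes, with few exceptions, are assessed before the intervention", and again at T1 and T2. Dietary diversity follows that schedule. Chair stand does not: footnote a to Table 2 says that the Senior Fitness Test measures "are assessed at T0 and T2 but not at T1".

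The Discussion lists recruitment after randomization as a limitation: "This may lead to recruitment bias and a discrepancy in the characteristics of the participants".

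**The concern.** The rule reads as a safeguard against unequal arms. In a model with T0 among the responses, the treatment effect is the difference between arms in change from T0. If chance puts one arm lower at T0, that arm tends to rise more by regression to the mean, and the change contrast absorbs this. A covariate that is constant over time shifts a person's T0 and T2 values equally, so it cannot touch that contrast. If the covariate is the T0 outcome itself, it also stands on both sides of the model, and the variance components no longer describe the data. Finally, the choice of model waits on the data.

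Both primary outcomes may be affected. At stake are protection that is not there, a possibly inflated type I error, and unused precision.

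**Working it through.** **Inputs.** From Sample size calculation and Data analysis: 300 + 150 participants, workshops of 10, intra-cluster correlation (ICC) 0.03, 30% dropout, α = 0.05 (two-sided assumed). Not in the documents and therefore assumed: within-person correlation ρ of 0.3 to 0.7, and outcome SD 1.

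**The plan's own figure.** No figure attaches to the adjustment rule. The stated 95% power can be neither confirmed nor refuted, because no effect or SD is given for chair stand. With 210 and 105 completers and design effect 1 + 6×0.03 = 1.18, SE = √[1.18(1/210 + 1/105)] = 0.130 SD. Then 95% power corresponds to (1.960 + 1.645)×0.130 = 0.47 SD, and a 1 SD effect gives about 100%. Nothing below depends on this.

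**1. Is T0 a response?** For chair stand only T0 and T2 exist. A time factor and a group-by-time term need two response times, so T0 must be one of them. For dietary diversity (T0, T1, T2) the stated model fits either reading.

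**2. Cancellation.** With a baseline term γX in the mean at each time, the change T2 − T0 contains γX − γX = 0. Simulation used 45 workshops of 10, 2:1, ICC 0.03, no true effect, and REML with workshop and participant intercepts (3,000 runs per main scenario). With complete data the estimates with and without the covariate differed by less than 1e-14. With 30% dropout they differed by 0.009 to 0.022 SD on average (0.1 to 0.2 SE). Their dependence on the baseline difference was the same: slope −0.353 in both at ρ = 0.5, two time points.

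**3. What stays uncorrected.** Without workshop effects, a chance T0 difference d biases the change contrast by −(1 − ρ)d. For d = 0.2 and ρ = 0.5 this is −0.10 SD, with or without the covariate. It is 0 when T0 is used only as a covariate (ANCOVA).

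If workshop effects persist from T0 to T2, they make up 10×0.03/(1 + 9×0.03) = 0.236 of the variance of a group mean. The within-workshop slope is (0.5 − 0.03)/0.97 = 0.485, and the group-mean slope is 0.236 + 0.764×0.485 = 0.606. The bias per unit of d is then −0.39 for the change contrast and about 0.606 − 0.485 = +0.12 for ANCOVA. The three-time-point simulation with complete data gave −0.403 and +0.100. ANCOVA then removes most of the bias, not all.

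**4. Standard error, two time points, T0 outcome as covariate, complete data.** The pooled slope is b = (1 + ρ)/2. The residual covariance between times is (1 − b)(ρ − b) = −(1 − ρ)²/4. This is negative, so a non-negative participant variance goes to zero, as it did in every run. The model then takes the variance of change as (1 − b)² + (ρ − b)² + 1 − ρ² = (1 − ρ)(3 + ρ)/2, against the true 2(1 − ρ). The SE ratio is √[(3 + ρ)/4] = 0.908, 0.935, 0.962 for ρ = 0.3, 0.5, 0.7. Type I error is 2[1 − Φ(1.96 × ratio)] = 7.5%, 6.7%, 5.9%.

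**5. Simulated standard errors.**

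| Case | SE with / without covariate | Type I error with covariate | Type I error without |
|---|---|---|---|
| Chair stand, complete, ρ = 0.3 / 0.5 / 0.7 | 0.908 / 0.934 / 0.960 | 7.5 / 7.1 / 5.8% | nominal in theory |
| Chair stand, 30% dropout | 0.82–0.83 | 10.7–11.6% | 4.1–5.4% |
| Dietary diversity, complete | 0.998–1.000 | 5.0–5.8% | 5.0–5.8% |
| Dietary diversity, 30% dropout (ρ = 0.3, 0.5) | 0.95 | 6.9–7.1% | 5.3–5.5% |
| Two times, unbounded compound symmetry, ρ = 0.5, complete (300 runs) | 1.000 | same as without | – |
| Same, 30% dropout (600 runs) | 0.86 | 10.0% | 4.8% |

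With T0 as covariate only, type I error was 4.5 to 5.3% in the main scenarios. Among runs with a marked T0 difference (|z| > 1.645), it was 7–18% unadjusted, 9–23% with the baseline covariate added, and 3–7% with T0 as covariate only.

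**6. Tests that ignore workshops.** At ICC 0.03 a nominal 5% test rejects with probability 2[1 − Φ(1.96/√(1 + 9×0.03))] = 2[1 − Φ(1.739)] = 8.2%.

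**7. Precision.** Before clustering and dropout, ANCOVA variance over change variance is (1 − ρ²)/[2(1 − ρ)] = (1 + ρ)/2 = 0.65, 0.75, 0.85. In the clustered simulations at ρ = 0.5 the gain was smaller. SE was 0.092 against 0.100 with complete data (variance 85%), and 0.110 against 0.115 with two time points and dropout (variance 91%).

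**The case against.** The details of the model are in Additional file 7, which is not shown, and the article never says that T0 is a response. This stands for dietary diversity: T1 and T2 could be the responses with T0 as covariate, and a group-by-time term would still exist. For chair stand the measurement schedule leaves no such room.

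The baseline values meant may be age, gender and life conditions, which are the only ones named for between-group testing. In that case nothing is on both sides and the standard-error problem falls away, but the cancellation remains. The same paragraph counts the primary and secondary outcomes among the baseline characteristics to be described, so the other reading is open too.

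Three stronger readings are tempting, and the documents do not support them:

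- That the standard error is too small whenever the rule is used. It is essentially unchanged for dietary diversity with complete data, and for two time points under unbounded compound symmetry with complete data. An unstructured covariance makes the model degenerate rather than overconfident. The dropout figures assume that incomplete data are modelled directly, whereas the article allows multiple imputation where appropriate. Exact cancellation also does not carry over to the logistic models.
- That the baseline tests trigger the rule. The article does not link them.
- That baseline adjustment cures recruitment bias. If the arms come from populations with a stable 0.2 SD difference and there is no effect, the change contrast is unbiased. ANCOVA is then off by 0.2×(1 − 0.5) = +0.10 SD. The Discussion's limitation is of this systematic kind, so the case for adjustment rests on chance imbalance and precision.

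**Conclusion.** The point holds in a limited form. For chair stand, and for dietary diversity if T0 is a response there, the conditional rule cannot do what it is there for. The estimate is the same with or without the covariate in a linear model with complete data, and nearly the same with dropout.

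The standard-error harm is conditional. It needs the T0 outcome as the covariate, and either two time points with a non-negative random intercept or dropout modelled directly. Under those conditions the type I error reaches about 11% for chair stand and about 7% for dietary diversity. These sizes rest on the assumed within-person correlations; the dietary diversity dropout runs cover 0.3 and 0.5 only.

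The undefined trigger is a separate weakness: the model for a primary outcome would be settled after the baseline data are seen.

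**What to change.** Delete the conditional rule and adjust for the T0 value of the outcome in every case, by one of two routes:

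- T0 as covariate only. Responses are T1 and T2 for dietary diversity, with T0 and T0-by-time as covariates, and T2 alone for chair stand, with T0 as covariate. The workshop effect is kept.
- T0 as a response, with the baseline means of the two arms constrained to be equal.

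State that no baseline significance test decides the model. If a baseline comparison is kept, report it descriptively. Say plainly that the adjustment deals with chance imbalance and not with systematic differences from recruitment after randomization.

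The cost is wording, settled before outcome data are examined; T0 is already collected. The one drawback is that, on the first route, missing T0 values need imputation.
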